**Sample size.**

**Phase 1:** The sample size for survey was calculated using the single population proportion formula,$$n=\frac{{\left(Z_{1-\frac{\alpha }{2}}\right)}^{2}pq}{{\left(d\right)}^{2}}$$

$Z_{1-\frac{\propto }{2}}$ = 1.96 at α = 0.05, *p* = Proportion, q = 1-p, d = allowable error (5% of p).$$n=\frac{{\left(1.96\right)}^{2}x\;\;0.61\left(1-0.61\right)}{{\left(.03\right)}^{2}}=317$$

Focus group discussions (FGDs) will be conducted until data saturation is achieved.

**Phase 2:** The sample size was derived using the formula for two independent groups,$$n=\frac{{\left(Z_{1-\frac{\alpha }{2}}+Z_{1-\beta }\right)}^{2}\sigma^{2}}{d^{2}},$$

$Z_{1-\frac{\propto }{2}}$ = 1.96 at α = 0.05, $Z_{1-\beta }$ = 0.84 at 80% power.

σ = Standard deviation difference of knowledge scores. d = Difference in pre- and post-intervention mean scores of knowledge.

The expected mean differences (d₁ = 2.26 and d₂ = 2.55) were derived from pilot observations conducted during preliminary implementation of similar training sessions.

To ensure a conservative and robust estimate, the average of the two values was considered for calculation:$$d=\frac{2.26+2.55}{2}=2.40$$

The pooled standard deviation was calculated using: $\sigma =\sqrt{\frac{\sigma_{1}^{2}+\sigma_{2}^{2}}{2}}$where:$$\sigma_{1}=20.7,\;\;\sigma_{2}=22.1\;\sigma =\sqrt{\frac{{\left(20.7\right)}^{2}+{\left(22.1\right)}^{2}}{2}}\approx 21.4$$

Substituting values into the formula:$$n=\frac{{\left(1.96+0.84\right)}^{2}\times {\left(21.4\right)}^{2}}{{\left(2.40\right)}^{2}}$$

The calculated sample size was 46 participants per group (*n* = 46), and an attrition rate of 10%, the required sample size per group is approximately 50 participants.

A total of 100 nurse researchers (50 in each group) who met the inclusion criteria were included in the second phase of the study.

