### Study variables

This study investigates the effects of a Mentored Writing Retreat Programme (MWRP) as the independent variable on several dependent variables. These dependent variables encompass Knowledge, Attitude, Publication Efficacy, and Publication Status. Through analysing these variables, the study aims to understand the impact of MWRP on participants' knowledge, attitudes, efficacy in publishing, and their actual publication status, offering insights into the effectiveness of such programs in enhancing scholarly productivity and publication success among researchers.

Operational Definitions•Knowledge: Knowledge refers to the participants’ understanding of the research publication process, including manuscript preparation, journal selection, and submission procedures. Score range 0–30; higher scores indicate better knowledge.•Attitude: Attitude refers to the participants’ perceptions, beliefs, and disposition towards research publication and engagement in scholarly writing activities.Score range 24–120; higher scores indicate positive attitude.•Publication efficacy: Publication efficacy refers to the participants’ self-reported confidence in their ability to successfully prepare, submit, and publish a research manuscript in indexed journals.Score range 12–60; higher scores indicate higher confidence.•Publication status: Number of manuscripts completed/submitted/published.

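### The Phase 2 sample size of 46 per group does not follow from the printed inputs, which give 624 (1,247 with the two-group formula), so the stated 80% power is unsupported

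*Protocol article*

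**What the plan says.** The Phase 2 part of the Sample size section introduces its calculation with "The sample size was derived using the formula for two independent groups". The formula printed after that is (Z for 1−α/2 plus Z for 1−β) squared, times σ², over d². The normal quantiles are "1.96 at α = 0.05" and "0.84 at 80% power".

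The two remaining inputs are defined as "σ = Standard deviation difference of knowledge scores" and "d = Difference in pre- and post-intervention mean scores of knowledge". On the source of d the section says: "The expected mean differences (d₁ = 2.26 and d₂ = 2.55) were derived from pilot observations". The two values are averaged to 2.40, and the average is described as conservative. The SDs of 20.7 and 22.1, for which no source is given, are pooled to about 21.4.

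The numbers are put into the formula, but the expression is not evaluated on the page. The next statement is "The calculated sample size was 46 participants per group", raised to about 50 per group for 10% attrition and 100 in total. Under Study variables, the knowledge outcome is defined with "Score range 0–30; higher scores indicate better knowledge".

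**The concern.** This calculation is the only justification offered for 50 per group. A reader can check the last step by hand, and it fails by a factor of more than 13 (623.3 / 46 = 13.6). The inputs also do not fit together: the formula's label, the definition of d and the size of the SD point to different designs or different scales.

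If the calculation stands as printed, readers will believe that the trial has 80% power to detect 2.40 points on the knowledge score, and nothing in the document supports that. A non-significant result would then be read against a sensitivity that was never shown. The article also offers itself as a model for others to replicate, so the calculation may be copied.

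**Working it through.** **Inputs** (Sample size, Phase 2, unless noted): Z values 1.96 and 0.84; d₁ = 2.26, d₂ = 2.55, d = 2.40; σ₁ = 20.7, σ₂ = 22.1, σ = 21.4; stated n = 46 per group; attrition 10%; knowledge scale 0 to 30 (Study variables).

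**1. The intermediate steps reproduce.** √((20.7² + 22.1²)/2) = 21.41, and (2.26 + 2.55)/2 = 2.405. Both agree with the printed values to within rounding.

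**2. The final step does not.** (1.96 + 0.84)² × 21.4² / 2.40² = 7.84 × 457.96 / 5.76 = 623.3, so 624 per group.

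**3. With the factor 2 for two independent groups.** n = 2(1.96 + 0.84)²σ²/d² = 2 × 623.3 = 1,246.7, so 1,247 per group.

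**4. Search for a reading that gives 46.**

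| Reading | Printed formula | With factor 2 |
|---|---|---|
| One-sided α | 492 | 984 |
| Either d or either SD taken alone, in any pairing | 517 to 750 | 1,033 to 1,499 |
| 21.4 taken as a variance | 29 | 58 |
| SD = 2.14 (misplaced decimal) | 6 | 12 |

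None gives 46. Baseline adjustment or a change-score analysis would need an unstated pre-post correlation of about 0.98 to bring 1,247 down to about 50. Working backwards from 46 with d = 2.40, the SD would have to be 5.8 in the printed formula or 4.1 in the two-group formula. With SD = 21.4 and 46 per group, the difference detectable with 80% power is 2.8 × 21.4 × √(2/46) = 12.5 points on a 30-point scale.

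**5. Power on the printed SD and d** (two-sided 5%, noncentral t).

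| n per group | Two-group comparison | Paired reading, no factor 2 |
|---|---|---|
| 45 | 8.2% | 11.4% |
| 46 | 8.3% | 11.6% |
| 50 | 8.6% | 12.2% |

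**6. Is the SD possible?** A score confined to 0–30 has its largest SD when half the people score 0 and half score 30. That SD is 15 (about 15.2 as a sample SD with n = 46). An SD of 20.7, 22.1 or 21.4 therefore cannot be a score SD on this tool. As an SD of pre-post change, 21.4 would need typical swings of about 20 points in opposite directions.

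**7. What plausible SDs would give.** The document reports no usable SD, so these are assumed values. For 2.40 points with 45 per group and no baseline adjustment:

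| Assumed SD | 4 | 5 | 6 | 7 |
|---|---|---|---|---|
| Power | 80% | 61% | 47% | 36% |

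With baseline adjustment at an assumed pre-post correlation of 0.5 to 0.7, the figure at SD = 6 rises to 58 to 75%. If 21.4 was meant as a variance (SD 4.63), unadjusted power is 68% at 45 per group and 73% at 50.

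**8. What 50 per group can detect.** 50 × 0.90 = 45 analysable. Unadjusted: 2.8 × √(2/45) = 0.59 SD. Adjusted for baseline: 0.59 × √(1 − 0.5²) = 0.51 SD, or 0.59 × √(1 − 0.7²) = 0.42 SD.

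**9. Attrition (minor).** 46 / 0.90 = 51.1, so 52 rather than about 50.

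**The case against.** The arithmetic in step 2 has no defence, but four objections to what is built on it deserve an answer.

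- **A reader might infer that the trial's power is really about 8%.** The documents do not support that. The figure uses an SD that the 0 to 30 scale rules out, and SDs of 4 to 7 give anything from 80% down to 36% before baseline adjustment. This objection stands: 8% shows that the printed inputs do not deliver 80%, and no more.
- **The missing factor 2 may be a wrong label.** With d a pre-post difference and σ apparently the SD of differences, the printed formula is the ordinary paired one, and the Data analysis section does plan within-group paired t-tests. This is a fair reading, and under it the figures are 624 and about 12% instead of 1,247 and about 8%. It does not yield 46, and it sizes a within-group test in a trial with a control group.
- **A pre-post change can stand in for the between-group difference**, because controls receive no intervention and might not change. That is reasonable if stated, but the protocol does not state it.
- **The SDs may come from another instrument.** The protocol links d to pilot observations of similar training sessions and gives no source for the SDs. A different scale, a variance or a misprint are all possible. The incompatibility with the 0 to 30 score is certain; its cause is not known.

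It would also be wrong to infer that the trial must enrol 1,247 per group. That number inherits the same impossible SD.

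**Conclusion.** The point holds and must be fixed. The stated 46 per group does not follow from the printed substitution under any reading tested; the correct evaluation is 624, or 1,247 for the design that the section names. This rests on nothing but the document's own numbers.

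The claim of 80% power for 2.40 points is unsupported, and the actual power is unknown, because no SD valid for the 0 to 30 scale is given. Without baseline adjustment the claim would be met at an SD of about 4; at larger SDs it would depend on a pre-post correlation that the document does not give either.

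Two lesser defects stand alongside. The effect is defined within group while the design compares groups. And the mean of 2.26 and 2.55 is called conservative although the smaller value would be the cautious choice; this is correct but of small consequence.

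**What to change.** 1. Trace the SDs of 20.7 and 22.1 and the differences of 2.26 and 2.55 to their source, and correct or re-express them on the 0 to 30 scale. Use the 30-person tool pilot if it yields a knowledge SD. Do not simply delete them.
2. Define d as the between-group difference, or state the assumption that controls do not change.
3. Recalculate with n = 2(z for α/2 + z for β)²σ²/d², and divide by 0.90 for attrition.
4. Withdraw the figure of 46, the 80% power for 2.40 points and the description as conservative, unless the corrected inputs bear them out.
5. If 50 per group is kept, say so openly and state what it delivers. With about 45 analysable per group, that is 80% power for about 0.59 SD in an unadjusted comparison. With the baseline adjustment that the Data analysis section plans, it is about 0.51 to 0.42 SD at an assumed pre-post correlation of 0.5 to 0.7.

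The cost is a correction to the text. If 50 per group is retained, no further participants are needed, but the stated detectable effect may become less favourable.

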**Methods:**

A participatory action research design will be adopted and implemented in two phases. **Phase I** will examine publication barriers and facilitators through a survey and focus group discussions among nurse researchers across Karnataka (*n* = 317). **Phase II** will use a quasi-experimental pre-test–post-test design with intervention and control groups (*n* = 50 per group). The MWRP will be developed based on Phase I findings and will include structured workshops, mentoring, and guided manuscript development over four months, followed by structured follow-up after six months post-intervention.

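### The Phase 2 sample-size equation as printed gives 623 per group, not 46, so the 80% power attached to 50 per group has no reproducible basis

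*Protocol article*

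**What the plan says.** The Phase 2 part of the Sample size section introduces the calculation with "The sample size was derived using the formula for two independent groups". The formula it then prints is the squared sum of the two z values, times σ², divided by d², with no factor 2. The z values are given as "1.96 at α = 0.05" and "0.84 at 80% power".

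The difference is defined by "d = Difference in pre- and post-intervention mean scores of knowledge". On its source, the article says: "The expected mean differences (d₁ = 2.26 and d₂ = 2.55) were derived from pilot observations". The two values are averaged and printed as 2.40. The SDs are 20.7 and 22.1, pooled to 21.4. After the full substitution comes the result: "The calculated sample size was 46 participants per group". A 10% attrition allowance takes this to about 50 per group, 100 in total, and the abstract repeats 50 per group.

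Under Study variables, the knowledge score is given a range of 0 to 30.

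**The concern.** The article does not merely cite a result; it sets out the arithmetic, and the last step does not evaluate to the number reported. The figure of 46 is the only stated basis for 50 per group and for the 80% power. If it does not follow from the inputs, the reader does not know what difference in knowledge the trial can detect, or with what probability.

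**Working it through.** **Inputs (Sample size section).** z = 1.96 and 0.84; d₁ = 2.26, d₂ = 2.55; σ₁ = 20.7, σ₂ = 22.1; stated n = 46 per group.

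**Intermediate steps.**
- Mean difference: (2.26 + 2.55)/2 = 2.405, printed as 2.40. Reproduces.
- Pooled SD: √((20.7² + 22.1²)/2) = 21.41, printed as 21.4. Reproduces.

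**Final step, as printed.**
- (1.96 + 0.84)² = 7.84; 21.4² = 457.96; 2.40² = 5.76.
- 7.84 × 457.96 / 5.76 = 623.3. The stated 46 is smaller by a factor of 623.3/46 ≈ 13.6. Does not reproduce.
- With the factor 2 of the usual two-group formula: 2 × 623.3 ≈ 1,247.

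**Can one change recover 46?**

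| Change to the printed calculation | n per group |
|---|---|
| d = 2.26 | 703 |
| d = 2.55 | 552 |
| One-sided 5% alpha | 492 |
| 21.4 read as a variance: 7.84 × 21.4 / 5.76 | 29 |
| SD read as 2.14 | 6 |

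None does.

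**Can several changes together?** Yes. With the factor 2, 21.4 as a variance and one-sided alpha (z = 1.645), 2 × (1.645 + 0.84)² × 21.4 / 2.40² = 2 × 6.175 × 21.4 / 5.76 = 45.9, which rounds up to 46. Working backwards, with the printed z values and d = 2.40, n = 46 needs σ = 2.40 × √46 / 2.80 = 5.8 without the factor 2, or 2.40 × √23 / 2.80 = 4.1 with it. Neither value is stated.

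**Is 21.4 possible as an SD?** On a score bounded by 0 and 30, the SD is largest when half the group scores 0 and half scores 30, which gives 15 (15.2 with the n − 1 divisor at n = 50). So 21.4 cannot be the SD of the score. The text's definition of σ could also mean the SD of a pre–post change. A mean change of 2.40 with an SD of 21.4 implies a root-mean-square change of √(457.96 + 5.76) = 21.5 points on a 30-point test, which only an extreme distribution could produce.

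**Power for a 2.40-point between-group difference (two-sided 5% two-sample t-test).**

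| Reading of 21.4 | SD | 46 per group | 50 per group |
|---|---|---|---|
| SD | 21.4 | 8.3% | 8.6% |
| Variance | √21.4 = 4.63 | 69% | 73% |

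On the variance reading, the two-sided normal formula needs 2 × 7.84 × 21.4 / 5.76 ≈ 58 per group for 80% power.

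**What the fixed size delivers.** 50 less 10% leaves 45 evaluable per group. The two-sided t-test then has 80% power for a difference of 0.597 SD, about 0.60 SD. Conversely, inflating 46 for 10% attrition gives 46/0.90 = 51.1, so 52 rather than 50; this is minor.

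**The case against.** The strongest reply is that the fault may lie in the printing and not in the design. The route to 45.9 keeps the article's d, its pooled 21.4 and its 80% power. It also restores the factor 2 that the named formula should have, and it implies an SD of 4.6, which is credible for a 30-item test. On that view, 46 was properly computed and only badly transcribed.

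Part of this stands. A reader might infer that no reading of the inputs can give 46; that is not so. But this route is only a possible origin. It changes three printed elements at once, one of which is the z value of 1.96, and other combinations also land near 46: 90% power, variance 22.1, d = 2.26 and no factor 2 give 45.4. Nor does it restore the power claim for a two-sided 5% test, which would have 69–73% power.

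It is also fair to say that knowledge is one of four outcomes listed without ranking, and that a null result would be read from its confidence interval and the observed SD. The error therefore does not by itself make a null result uninterpretable.

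**Conclusion.** The point holds: the printed calculation gives 623 (about 1,247 with the factor 2), not 46, and the 80% power for 50 per group does not follow from it. This part needs no assumption, since every number is in the text.

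Two stronger conclusions are tempting, and the document supports neither. One is that the trial needs 623 or 1,247 per group; those figures inherit an SD that the score cannot have. The other is that the trial really has about 8% power; that rests on the same SD. The true power is undetermined: about 8% if 21.4 is taken at face value as an SD, about 69–73% if it is a variance, and something else if the SDs come from another scale. The power figures assume a two-sided 5% comparison of two independent groups with a true difference of 2.40 points.

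The section must be corrected, because it is the only stated justification for the trial's size.

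**What to change.** 1. Go back to the source of 20.7 and 22.1 and establish whether they are SDs or variances, of a score or of a change, and on which scale.
2. State whether alpha is one- or two-sided, and either restore the factor 2 or explain why it is absent.
3. Reprint a two-group calculation that reproduces, using an SD for the actual 30-item knowledge test. The tool pilot of 30 nurse researchers (Description of the tool) may supply one if its scores were kept; the article reports only reliability from it.
4. Delete 46 as a derived figure and state what the fixed size delivers. Suggested wording: with 50 per group and 10% attrition, 45 evaluable participants per group give 80% power, at two-sided 5%, for a between-group difference of about 0.60 SD, equal to X points on the 0–30 knowledge score. X is to be filled in from the verified SD.

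This is a change of text with no extra enrolment. The cost is that the stated sensitivity may become less favourable: with an SD of 4.63, for example, 0.597 SD is about 2.8 points rather than 2.40.

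### Fifty per group does not cover the stated 10% attrition from 46: it leaves 45 evaluable and allows for 8% loss, a minor shortfall on a base figure that itself needs reconciling

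*Protocol article*

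**What the plan says.** The protocol article, under Sample size (Phase 2), sets a two-sided 5% level (z = "1.96 at α = 0.05") and a power term of "0.84 at 80% power". It reports the result as "The calculated sample size was 46 participants per group". It then names an attrition rate of 10% and concludes that "the required sample size per group is approximately 50 participants". The next sentence turns this into an exact enrolment: "A total of 100 nurse researchers (50 in each group"). The Abstract and the recruitment and allocation text also give 50 per group. The article does not say which formula took 46 to 50.

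**The concern.** An attrition allowance is meant to leave at least the calculated number once the expected loss has occurred. Here the loss rate, the number needed and the number enrolled are all stated, and they do not fit together: a 10% loss from 50 leaves fewer than 46. The requirement was rounded down where it should be rounded up. At stake is whether the enrolled number supports the 80% power claimed, on the protocol's own figures.

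**Working it through.** **Inputs**, all from Sample size, Phase 2: 46 per group before attrition; attrition 10%; 50 per group enrolled; z values 1.96 and 0.84; standard deviation 21.4; difference 2.40.

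**1. The attrition step, taking 46 as given**

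- Inflation by n/(1 - loss): 46/0.90 = 51.1, rounded up to 52 per group. Check: 52 x 0.90 = 46.8, which is at least 46; 51 x 0.90 = 45.9, which is not.
- Shortcut n x (1 + loss): 46 x 1.10 = 50.6, rounded up to 51.
- What 50 delivers: 50 x 0.90 = 45.
- Loss that 50 can absorb: 1 - 46/50 = 0.08, or 8%.

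The stated 50 is reached only by rounding 50.6 or 51.1 down.

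**2. What one participant per group costs in power**

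Suppose 46 per group gives exactly 80%. The normal-approximation argument scales with the square root of n, so at 45 per group:

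(1.96 + 0.84) x sqrt(45/46) - 1.96 = 2.80 x 0.9891 - 1.96 = 0.809

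This corresponds to a power of about 79.1%, a loss of about 0.9 percentage points. The result needs only the assumption that 46 gives 80%. It does not depend on any particular difference or standard deviation.

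**3. Whether 46 itself can be reproduced**

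The printed substitution is (1.96 + 0.84)^2 x 21.4^2 / 2.40^2:

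7.84 x 457.96 / 5.76 = 623.3, so 624 per group, not 46.

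The section says that "The sample size was derived using the formula for two independent groups", but the printed expression lacks the factor 2 that this comparison carries. With it, the same inputs give 2 x 623.3 = 1,246.7, so 1,247 per group. For 46 to follow with a difference of 2.40, the standard deviation would have to be:

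- formula as printed: sqrt(46 x 5.76 / 7.84) = 5.8;
- with the factor 2: sqrt(46 x 5.76 / 15.68) = 4.1.

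With the printed 21.4 and 2.40, two-group power at 45 per group is about 8%: 2.40 / (21.4 x sqrt(2/45)) = 0.53, and 0.53 - 1.96 = -1.43, which corresponds to 0.077.

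**The case against.** The strongest reply is that this is only rounding. The text says approximately, the inflation convention is not given, the gap is one or two people per group, and 10% is a planning guess. All of that bears on the size of the point and is accepted. It does not remove the point, because the next sentence fixes the enrolment at exactly 50 per group and neither usual convention, rounded up, gives 50.

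A second reply is that adjusting 46 by a few people misses the larger problem, since 46 does not follow from the printed inputs. That stands, and it sets the order of the correction. It does not make 46, 10% and 50 consistent with each other.

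Two stronger readings are tempting.

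- *Power falls to about 78%.* A reader might exchange the labels, taking 20.7 and 22.1 as means (difference 1.4) and 2.26 and 2.55 as standard deviations (pooled 2.41). The two-group formula then gives 2 x 7.84 x 2.409^2 / 1.4^2 = 46.4, and power at 45 per group comes out at 78 to 79%. The knowledge score runs from 0 to 30, which makes a standard deviation of 21.4 implausible and the exchange a reasonable guess. But the document labels the values the other way ("The expected mean differences (d₁ = 2.26 and d₂ = 2.55) were derived from pilot observations") and substitutes them that way. Even on the exchanged reading, going from 46 to 45 costs only about 0.9 points; the rest of the gap to 80% comes from rounding 46.4 down and from using t instead of z.
- *The trial must enrol 52 or 53 per group.* The right target cannot be known until the base is settled. The section also reports the 100 participants as already included, although the allocation text is written in the future tense, so enlarging the groups may not be possible.

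**Conclusion.** Wrong as written, and minor. On the protocol's own 46 per group, an enrolment of 50 allows for 8% attrition and not the stated 10%. The shortfall is one evaluable participant per group, or one to two enrolled per group (51 or 52 against 50). The cost is about 79% power instead of 80%, on the assumption that 46 truly gives 80%. The printed inputs do not support that assumption, so no absolute power figure for 45 per group should be drawn from this paragraph. The point concerns the consistency of the three stated numbers only. It does not show that the trial needs more participants.

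**What to change.** 1. Reconcile the standard deviation, the difference and the formula (including the factor for two groups) so that the base number follows from what is printed.
2. Restate the attrition allowance from the corrected base as n/(1 - 0.10), rounded up. Fifty per group covers 10% loss only if the corrected base is 45 or fewer (50 x 0.90 = 45).
3. If 46 is confirmed, keep 50 per group and say either that it allows for 8% attrition from 46, or that 45 per group remain after 10% attrition. Do not quote a 78% power figure beside inputs that do not produce it.

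The attrition correction costs one sentence and no extra recruitment, and the stated allowance becomes slightly less favourable. Step 1 is the larger piece of work, but the same paragraph has to be revised for it in any case.
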